##### Secondary outcomes

Longitudinal anxiety scores at 3 and 6 months will be analysed in the same way as the primary anxiety outcome.

Differences in understanding score between communication methods groups will be assessed using a logistic regression model, adjusting for fixed effects.

Outcome variable—subjective understanding score (binary—yes or no), objective understanding score (binary—right or wrong).Fixed effects—age, ethnicity, previous attendance, previous biopsy, education, marital status.Comparator variable—method of communication received (telephone/in-person).

Preference data from the quantitative surveys will be presented in the form of percentages. All analyses will be implemented using IBM SPSS Statistics V.25.

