## Methods and analysis

### Study design

The study design chosen was a multi-centre cluster randomised crossover trial. The randomisation allows for the direct comparison of study outcomes between women who received telephone results and women who received in-person results, while controlling for confounding factors such as education, age and individual differences in baseline anxiety.

Patient and public involvement from the charity Independent Cancer Patients’ Voice was used to guide the design of the study to ensure the acceptability of the method and appropriateness of the participant materials.

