### Participants and settings

This trial will be conducted in a breast screening centre setting. The study will take place in the UK where women are invited to attend breast screening every 3 years for digital mammography. The study will take place across four time points (see table 1) with a survey completed by participants at each stage. The study participants will be recruited from four English Breast Screening centres across different regions.

**Table 1 T1:** Time points for the study

Time point	Sample	Survey content	Method
Time point 1—at assessment clinic	Women attending assessment follow-up clinic	Demographic information Communication preferences Baseline anxiety score (PCQ) Contact details	In-person
Time point 2—after receiving results	Women from time point 1 who had a normal or benign biopsy	Communication preferences Repeat anxiety score (PCQ) Measure of understanding	By post
Time point 3—3-month follow-up	Women from time point 1 who had a normal or benign biopsy	Repeat anxiety score (PCQ)	By post
Time point 4—6-month follow-up	Women from time point 1 who had a normal or benign biopsy	Repeat anxiety score (PCQ)	By post

PCQ, Psychological Consequences Questionnaire.

Participants will be women between the ages of 47 and 73 attending the NHSBSP for further tests following a suspicious mammogram. This includes women offered routine screening between ages 50 and 70 and those receiving extra rounds of screening between the ages of 47 and 49 or 71 and 73 as part of the UK age extension trial.^16^ Women will be recruited at the assessment clinic pre-biopsy. However, only women who have received a benign (B2) or normal (B1) biopsy result will be included in the longitudinal data collection. Participants will not be included in the study if they presented symptomatically to the breast clinic, if they are not the recommended screening age, if they do not receive a biopsy, if they do not have English as a first or second language and if they do not have the capacity to consent.

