### Randomisation and blinding

Each centre will be randomised to one of two intervention arms by computer generated random numbers from the trial team base at the University of Warwick (see table 2). The arm relates to whether the first month at each centre will be telephone or in-person results. Each centre will commence with the communication method randomised in month 1 and continue to alternate between the two communication methods for the duration of the study. This approach allowed for each centre to use both methods of communication, controlling for previous experience (eg, centres who already telephone are more experienced and therefore women receiving telephone results from this centre might be less anxious).

**Table 2 T2:** Allocation of communication method by arm of the trial

Month	Arm 1	Arm 2
1	Telephone	In-person
2	In-person	Telephone
3	Telephone	In-person
4	In-person	Telephone
5	Telephone	In-person
6	In-person	Telephone

This approach was selected instead of a block approach, where each centre would deliver 6 months in-person followed by 6 months of telephone. The reason for this was to avoid potential bias from unforeseen centre drop out.

This design was chosen to ensure balance between trial arms at each site while addressing practical constraints. Balance between trial arms at each site is important to account for centre-level confounders such as staff communication skills and centre-level processes.

Individual randomisation was not possible as it interfered with screening centres workflow and fail-safe mechanisms to ensure that every woman was contacted with the correct information within the correct time frame.

Women will be allocated to receive their result based on the date of their attendance at the assessment visit. However, participants will be blinded to the randomisation month. Participants will only become aware of the communication method allocated when the results are received (see ‘Allocation of communication method’ section below for further detail). Breast screening staff will not be blinded, as they will be delivering the results and scheduling the appointments.

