**Figure 1 F1:**
[figure not shown]
Flow of required sample size for the study.

Assuming the primary outcome is approximately normally distributed, and the test is at the 5% significance level with 80% power to detect an effect of the specified size, 194 participants are required at time point 2, that is 97 participants per arm. Allowing for attrition rate between time point 1 and time point 2 due to participant withdrawal (15%) and participant eligibility (50%), a total of 457 participants will be recruited at time point 1. Participant withdrawal was calculated based on a mean response rate of 60% from previous research using postal surveys in a medical setting^24^ with a loss of 15% at each time point as a conservative estimate.

In order to account for clustering due to the recruiting centre, design effect was applied that inflated the sample size. The intra-cluster (within-centre) correlation coefficient was set to be 0.01 and the number of observations within each cluster was assumed to be equal. With the sample size of 194 women, divided by the number of centres^4^ and then divided by the number of interventions,^2^ this led to the number of observations within a cluster to be 48.2. This gave a design effect of 1.49. Taking this into account, the sample size needed to achieve statistical significance (194 women) was multiplied by the design effect, giving a total sample of 290 women at time point 2 when rounded up (see figure 1).

31 926 women are recalled for a biopsy each year. If half of the 31 926 biopsies come back as benign, this leaves a potential sample of 15 963. This means that, on average across 80 breast screening centres, each centre will have around 200 benign biopsy results each year. Therefore, assuming 50% participation rates of eligible women, recruitment will require four centres for 1 year.

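### The logistic models for understanding omit the centre and period terms used for the PCQ, so their standard errors ignore allocation by centre-month; the error is small and its direction is not fixed

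*Protocol article*

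**What the plan says.** Under Analysis, Secondary outcomes, subjective and objective understanding are each binary, and the method is given as "Differences in understanding score between communication methods groups will be assessed using a logistic regression model, adjusting for fixed effects". The covariate line reads "Fixed effects—age, ethnicity, previous attendance, previous biopsy, education, marital status", and the only other term is the communication method received. Neither centre nor period appears there, and there is no random-effects line.

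The primary analysis lists the same six covariates, adds the baseline PCQ, and has random effects for centre and period. The Secondary outcomes section says that PCQ at 3 and 6 months is analysed like the primary outcome, so those models keep both terms. Understanding alone has a specification without them.

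The design sections say "The study design chosen was a multi-centre cluster randomised crossover trial" and "The study participants will be recruited from four English Breast Screening centres across different regions". On allocation: "Each centre will commence with the communication method randomised in month 1 and continue to alternate between the two communication methods". The sample size section assumes a within-centre ICC of 0.01 and zero correlation between periods.

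**The concern.** The unit of allocation is the centre-month, but the understanding models treat each woman as an independent observation. Two women assessed in the same centre and month share staff, local procedures and the communication method. The article accepts this for anxiety, where it both inflates the sample size and adds random effects, but not for two outcomes taken from the same time point 2 survey.

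Two things are at stake. The first is the standard error: the reported intervals and p-values do not reflect how the methods were allocated. The second is the comparison itself. If a centre contributes more women under one method than under the other, a model without a centre term lets differences between centres leak into the estimated effect of method. How clearly a result is explained could plausibly differ between centres.

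**Working it through.** **Inputs from the article.** 290 women at time point 2; four centres; ICC ρ = 0.01; between-period correlation η = 0; two-sided 5% test (sidedness assumed). Duration: "recruitment will require four centres for 1 year", so 12 monthly periods; Table 2 displays six.

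**Inputs assumed.** The article gives no ICC for understanding, no proportion answering yes or correctly, and no split of centres between the two arms. I vary ρ from 0.01 to 0.05 and η from 0 to ρ.

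**The article's own figure.** 194 × 1.49 = 289.06, rounded up to 290. With the stated cluster size of 48.2, 1 + 47.2 × 0.01 = 1.472, which gives 286 women; the stated 1.49 corresponds to a cluster size of 50. The 290 is thus reproduced closely enough to use here. How the cluster size was derived is a separate matter.

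**Cluster size for this design.** 4 centres × 12 months = 48 centre-months; 290 / 48 = 6.04 women each. With six months, 290 / 24 = 12.08.

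**Formula.** For equal centre-month sizes m, the true variance of the method contrast divided by the variance under independence is V = 1 + (m − 1)ρ − mη. The last term is the credit for the crossover. The true standard error is √V times the naive one, and a nominal 5% test has true type I error 2 × [1 − Φ(1.96 / √V)].

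| Periods | m | ρ | η | V | True SE / naive SE | Type I error |
|---|---|---|---|---|---|---|
| 12 | 6.04 | 0.01 | 0 | 1.050 | 1.025 | 5.6% |
| 12 | 6.04 | 0.01 | 0.005 | 1.020 | 1.010 | 5.2% |
| 12 | 6.04 | 0.01 | 0.01 | 0.990 | 0.995 | 4.9% |
| 12 | 6.04 | 0.05 | 0 | 1.252 | 1.119 | 8.0% |
| 12 | 6.04 | 0.05 | 0.025 | 1.101 | 1.049 | 6.2% |
| 12 | 6.04 | 0.05 | 0.05 | 0.950 | 0.975 | 4.4% |
| 6 | 12.08 | 0.01 | 0 | 1.111 | 1.054 | 6.3% |
| 6 | 12.08 | 0.05 | 0 | 1.554 | 1.247 | 11.6% |

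Rows with η = 0 put all correlation within the centre-month. Rows with η = ρ make it a stable centre effect, which cancels in the within-centre contrast but still sits in the naive variance.

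**Simulation check.** Unadjusted logistic Wald test, 290 women, four centres, assumed 80% event rate, 8,000 runs per setting, effects added on the log-odds scale. Over 12 months:

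- stable centre effect: 4.6–4.8% at ICC 0.01 and 4.3–4.5% at 0.05;
- centre-month effect: 5.0–5.6% at 0.01 and 6.1–6.8% at 0.05;
- month effect shared by all centres at 0.05: 4.5% if centres split 2:2 between arms, 6.4% if each centre is randomised independently, 11.6% if all four fall in one arm.

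Over six months a centre-month effect gives 5.4–5.8% at 0.01 and 8.1–8.5% at 0.05. The simulation confirms both directions, with a smaller inflation than the formula at 0.05.

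**The case against.** The strongest objection is that the omission does little harm. The crossover already balances methods within centres, as the article says: "Balance between trial arms at each site is important to account for centre-level confounders such as staff communication skills and centre-level processes". That sentence describes protection by design and does not mention understanding. With monthly alternation, stable centre differences largely cancel, and at the only ICC the article gives the standard error is off by between −0.5% and +2.5% over 12 months. The outcomes are secondary. All of this stands and limits the weight of the point. It does not remove it, because the balance is approximate and the data are still analysed as if women had been allocated individually.

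A second objection is that the article defers detail to a later SAP. It does, but it also writes out every term of these models, so an SAP that followed it would carry the omission forward.

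Three stronger readings are tempting and are not supported:

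- *The intervals are always too narrow.* A stable centre effect makes them slightly too wide.
- *Type I error is 9% to 24%, or about 11%.* The first pair needs women to be correlated across all of a centre's months under one method (m = 290 / 8, about 36) but not with that centre's other months: V = 1.35 at ICC 0.01 and 2.76 at 0.05. That is a centre-by-method interaction, which nothing in the article quantifies and which centre and period terms would not remove. The figure of about 11% (10.8%) applies the design effect of 1.49, which gives no credit for the crossover and uses far larger clusters than a centre-month.
- *The within-centre contrast is discarded, or the comparison is shown to be biased.* Near-balance by design keeps most of the contrast, and the article has no month-by-month numbers from which to size any imbalance.

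**Conclusion.** The point holds as an inconsistency with small to moderate consequences. The understanding models are specified without centre or period, although allocation is by centre-month and every PCQ model includes both. Their standard errors are therefore wrong, in a direction that the article does not determine.

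At its own ICC of 0.01 and 12 monthly periods, true type I error lies between about 4.9% (stable centre effect) and 5.6% (centre-month correlation). At an assumed ICC of 0.05 the range is about 4.4% to 8.0%. If only the six months shown in Table 2 were run, the upper ends would be 6.3% and 11.6% by formula.

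These figures assume equal centre-month sizes and, for the formula, no month effect shared across centres. A shared month effect matters only if the arms are unbalanced. The article says "Each centre will be randomised to one of two intervention arms by computer generated random numbers" and states no 2:2 split; with independent randomisation all four centres would fall in one arm with probability 2 × (1/2)⁴ = 12.5%. Chance imbalance of methods within centres is a further exposure that cannot be sized from the article.

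**What to change.** Carry centre and period terms into both understanding models, so that they respect the same design as the PCQ analyses. Either of two forms would do:

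- a mixed-effects logistic model with random centre and centre-by-period effects; or
- centre as a fixed effect (three extra parameters) with a random centre-month intercept.

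The second avoids estimating a variance from four centres. In either case name a small-sample method for inference, and state in advance which term is dropped if the model does not converge.

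Do not enter calendar month as a set of fixed effects without checking the split of centres between arms: if all four had the same sequence, month would be completely aliased with method.

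The cost is a few lines in the SAP and a slightly more complex model, with a real chance of convergence trouble for a binary outcome in centre-months of about six women. No new data or software are needed.

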#### Qualitative data analysis

Qualitative preference data from time point 1 and time point 2 surveys and data from the telephone interviews will be analysed using inductive thematic analysis,^25^ managed using NVivo V.10.

### Mixed-methods integration

To integrate the quantitative and qualitative preference data, the pillar integration process will be used.^26^ This analytical integration technique uses four systematic stages (listing, matching, checking and pillar-building) to identify and examine connections and discrepancies in qualitative and quantitative findings. It allows for the visual display of the data and findings; this enhances overall transparency of the integration approach and the results of such an integration.

### Ethics

Attention was given to the various ethical challenges of the trial. The main ethical issue will be the use of sensitive patient information (addresses, telephone numbers). Participants will be told explicitly how their contact details will be used and stored throughout the data collection process. Participants will give informed consent for their contact details to be used for the purposes of the study.

All electronic data will be transferred securely in a password protected excel document from secure email accounts. All raw survey data will be collected directly from the centres by the lead researcher and be transferred in a secure lock-box.

### Dissemination

Results from the trial will be disseminated directly to key stakeholders within the NHSBSP. This will encourage discussion regarding how benign results are communicated in breast screening, and how this might best be implemented in order to minimise the anxiety women experience.

The results will also be disseminated via academic publications.

### Current study status

The trial began recruitment in February 2018. Data collection is due to conclude in March 2019. The trial statisticians (SW and NP) have received recruitment data but no results will be transferred to the statisticians until recruitment is closed in March 2019.
